#### Univariable analysis

We will calculate standardized differences for the variables of interest for the patient population with and without atrial fibrillation.

#### Regression modeling (aim 1)

a) The study index date will be the date of the first AF claim in the study and July 1 in the first year of inclusion in the analytic cohort for controls for the purposes of our survival analysis.b) We will describe cumulative incidence of CRAO over time with the overlap-weighted cumulative incidence function and presented graphically for patients with and without atrial fibrillation. Next, a weighted, unadjusted cause-specific hazard model will be fit with AF as the univariable predictor and CRAO as the event of interest, with patients censored at death, at end of data availability, or at end of fee-for-service Medicare enrollment.c) Then, a weighted cause-specific hazard model, clustered by state, and adjusting for age, sex, race, cardiovascular comorbidities will be fitted. Directly adjusted cumulative incidence curves for AF and control patients will be created with adjustment for all model covariates [28].d) We will test the proportional hazards assumption for all models.e) Our primary analytical model will be an overlap-weighted model with propensity scores derived from the adjustment covariates previously described as predictors for the presence of atrial fibrillation. We will report our results with sequential adjustment to produce the fully-adjusted, weighted model. We employ this sequential adjustment strategy to provide insight as to sources of measured confounding.f) We will evaluate **positive control endpoints**. Our positive control endpoints will be any ischemic stroke (defined by ICD-9-CM 434.0, 434.00, 434.10, 434.11, 434.9, 434.90, 434.91, 436/ ICD-10-CM I66.09, I66.19, I66.29, I66.9, I63.40, I63.50, I67.89 in the primary diagnosis position in a hospitalization or ED visit) [29]. We will utilize the same modeling strategy as used for the primary outcome.g) We will evaluate **negative control (falsification) endpoints**. Our negative control endpoint will be hospitalized/ED urinary tract infection (including renal abscess and pyelonephritis) (ICD-9-CM 590.1, 590.11 590.2, 590.8 or 599.0/ ICD-10-CM N15.1, N39.0, N10). We will utilize the same modeling strategy as used for the primary outcome [30].h) We will perform several sensitivity analyses for outcome ascertainment.
1) We will repeat the primary analysis, classifying CRAO based on the presence of the ICD codes in any diagnosis position rather than the primary diagnosis position.2) We will perform a sensitivity analysis for any retinal artery occlusion, using ICD-9-CM codes 362.3, 362.30, 362.31, 362.32, 362.33 and ICD-10-CM codes H34.9, H34.233, H34.1x, H34.0x, H34.12, H34.13, H34.23x, H34.21x) [31].i) We will perform a secondary analysis of patients with CRAO who later developed atrial fibrillation, to assess the hypothesis that clinically undetected paroxysmal AF may be associated with CRAO.j) Table shell for Aim 1 regression results are provided in Tables 6 and 7. The primary outcome is underlined.k) To address confounding resulting from patients potentially receiving a competing therapy (left atrial appendage occlusion, a procedural alternative to long-term oral anticoagulation), we will exclude patients with ICD-9-CM procedure code 37.90 or ICD-10-CM 02L73DK either in the follow-up period or in the ascertainment period.

**Table 6 pone.0296251.t006:** Crude and adjusted rates of CRAO in patients with and without atrial fibrillation.

	AF		No AF		AF	No AF	Rate Difference (95% CI)	aHR (95% CI)
	Patients with event	Rate per 1000 Or 100,000 Person-years	Patients with event	Rate per 1000 Or 100,000 Person-years	Adjusted rate per 1,000 person-years	Adjusted rate per 1,000 person-years		
CRAO (Overlap weighted)								
CRAO (primary Dx)								
Any RAO								
Ischemic stroke								
UTI								

**Table 7 pone.0296251.t007:** Hazard ratios for atrial fibrillation vs. no atrial fibrillation for Aim 1.

Outcome	Unadjusted Model	Adjusted Model†
CRAO (Overlap weighted)	HR (95% CI)	aHR (95% CI)
CRAO (primary dx)	HR (95% CI)	aHR (95% CI)
Any RAO	HR (95% CI)	aHR (95% CI)
CRAO (any dx position)	HR (95% CI)	aHR (95% CI)
Ischemic Stroke	HR (95% CI)	aHR (95% CI)
UTI	HR (95% CI)	aHR (95% CI)

^†^This column reflects the results of a model that incorporates overlap weighting using propensity scores re-estimated after our first stage matching procedure.

We will report a figure showing the adjusted cumulative incidence of CRAO according to AF vs. No AF groups using an overlap-weighted cumulative incidence function.

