### Inclusion and exclusion criteria (Aim 1)

The inclusion criterion is continuous fee-for-service Medicare enrollment for at least 12 months prior to AF diagnosis or matched index date (July 1 of inclusion year) for controls and continuous enrollment in fee-for-service (FFS) Medicare after AF diagnosis/index date for at least 12 months or until death if death occurred before 12 months of continuous enrollment.

Patients with prevalent AF will be identified as follows:ICD-9-CM code 427.31 or ICD-10-CM code I48 in 2 outpatient claims or 1 inpatient claim within 365 days, in any diagnosis position of the claim [16–18]. The index date will be the date of the first qualifying inpatient claim or second qualifying outpatient claim. Patients will be required to have 12 months of FFS claims without an AF diagnosis prior to the index AF claims based on inclusion criteria.

Exclusion criteria are:

patients with any claim for CRAO in the 12 months prior to AF diagnosis or index date for controls (July 1 of potential inclusion year).

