### Analytical cohort

An analytic cohort will be generated by applying the below inclusion and exclusion criteria as follows:

All patients meeting the criteria for AF in the study period and meeting other inclusion/exclusion criteria will be identified as cases, and the date of AF diagnosis will serve as case’s index date for calculation of covariates. All remaining beneficiaries will be considered potential controls; inclusion and exclusion criteria will be applied based on an index date of July 1 for each year in the study period; all beneficiaries meeting inclusion/exclusion criteria for each year will be included in the potential control pool. For all potential controls with multiple index dates/years of eligibility, the year they contribute will be selected randomly. A multivariable logistic regression analysis will be conducted using cases and potential controls to create propensity scores for AF status; the final control group will be selected using propensity score matching to the AF cases.

Survival time for patients will be defined as the number of months from the index date when criteria were met. Patients will be censored at death, at the end of fee-for-service enrollment, or at the end of data availability. When 85% of the cohort has died or been lost to follow-up, we will censor remaining patients at that point to avoid instability in estimates due to very small numbers of remaining participants.

Details of the cohort analysis will be reported using RECORD guidelines for analyses of routinely collected data, including use of a patient flow diagram [24].

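### The Aim 1 survival section starts AF follow-up at the first AF claim, while the eligibility and cohort sections start it at the qualifying claim; control time zero is also worded ambiguously

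*Protocol article*

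**What the plan says.** **AF patients.** Inclusion and exclusion criteria (Aim 1) accepts one inpatient claim, or two outpatient claims within 365 days, and then states: "The index date will be the date of the first qualifying inpatient claim or second qualifying outpatient claim". Analytical cohort agrees on the clock: "Survival time for patients will be defined as the number of months from the index date when criteria were met". It also says that "the date of AF diagnosis will serve as case’s index date for calculation of covariates". Regression modeling (aim 1), item a, gives a different start: "The study index date will be the date of the first AF claim in the study". The same sentence says that it applies to the survival analysis.

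**Controls.** Analytical cohort tests eligibility at July 1 of every year and says of beneficiaries with several eligible years that "the year they contribute will be selected randomly". Regression modeling (aim 1), item a, uses "July 1 in the first year of inclusion in the analytic cohort for controls for the purposes of our survival analysis". Adjustment covariates counts the look-back from July 1 of the initial inclusion year, and the title of Table 3 places baseline at the earliest date on which eligibility was met.

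**Prior CRAO.** The Aim 1 exclusion covers any CRAO claim in the 12 months before AF diagnosis, or before the index date for controls. It does not say whether AF diagnosis means the first or the qualifying claim.

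**The concern.** Time zero of the primary analysis has two definitions in the AF arm. A patient with one outpatient AF claim joins that arm only by surviving, and staying observable, until a second claim. If the clock starts at the first AF claim, the interval counts as AF follow-up although membership of the group was settled at its end. Controls have no corresponding interval. If CRAO in the interval also leads to exclusion, person-time is added with no possible event, and the AF rate and hazard ratio fall. Covariates may be misaligned too: a 12-month look-back from the qualifying claim would cover time that item a already treats as follow-up.

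The control wording raises the same question in the other direction. If the clock starts at the first eligible year while the control contributes a later, randomly drawn year, some control time is event-free by design and the hazard ratio rises. Two analysts who each follow the text could obtain different primary estimates.

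**Working it through.** The plan gives no figure for this point: no share of AF patients with a gap, no length of gap and no mean follow-up. It does give the 365-day limit (Inclusion and exclusion criteria, Aim 1) and the hazard ratio of 2 (Sample size calculation), used here as the reference value.

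**1. Who is affected.** Patients whose first AF claim is the qualifying inpatient claim have the same date under both rules. For patients who qualify on two outpatient claims, the dates differ by up to 365 days.

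**2. What cannot happen in the gap.** Death before the second claim would prevent entry, so the gap is immortal for death. For CRAO it depends on the exclusion. If AF diagnosis is the qualifying date, the 12-month exclusion window covers the gap and CRAO there removes the patient. If it is the first AF claim, CRAO in the gap counts as an event and the dilution in step 3 does not apply.

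**3. AF arm, with gap CRAO excluded.** Let T be mean follow-up after the qualifying claim, f the share of AF patients with a gap and g its mean length. With constant hazards, events arise over T but the rate is divided by T + f·g:

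observed HR = true HR × T / (T + f·g)

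| f | g | T | Observed HR when the true HR is 2 |
|---|---|---|---|
| 0.5 | 1 month | 3 years | 6 / 3.042 = 1.97 |
| 0.5 | 3 months | 3 years | 6 / 3.125 = 1.92 |
| 0.5 | 6 months | 3 years | 6 / 3.25 = 1.85 |
| 0.5 | 3 months | 1 year | 2 / 1.125 = 1.78 |
| 1 | 12 months | 3 years | 6 / 4 = 1.50 |
| 1 | 12 months | 1 year | 2 / 2 = 1.00 |

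The values of f, g and T are assumptions. The last two rows are extremes: every AF patient with the longest permitted gap.

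**4. Controls, if the clock starts at the first eligible year.** Assume k consecutive eligible years, one drawn with equal probability, and 5 years of follow-up after the drawn date. The mean shift is (k − 1)/2 years. Only CRAO in the 12 months before the drawn date excludes, so each control has at most one event-free year. A share (k − 1)/k of controls has a shift, so the mean event-free time is (k − 1)/k years.

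- k = 5: total time 5 + 2 = 7 years, event-free 0.8 year; 7 / (7 − 0.8) = 1.13.
- k = 10: total time 5 + 4.5 = 9.5 years, event-free 0.9 year; 9.5 / (9.5 − 0.9) = 1.10.

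The control rate is divided, and the hazard ratio multiplied, by about 1.1.

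**The case against.** The survival section may use first AF claim loosely for the qualifying claim, and two of the three relevant sections already agree. That is possible, but item a is the sentence written for the survival analysis, so it is the one a programmer would be expected to follow. Its literal meaning differs from the eligibility rule. This is a conflict between stated rules, not a detail left to a fuller document.

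The control half is weaker, and this objection largely stands. Each control contributes one year, so the first year of inclusion in the analytic cohort can simply be the drawn year. Adjustment covariates uses similar wording for the look-back, so on the first-eligible-year reading that section and the survival clock share a date. The title of Table 3 is harder to read this way, and no section settles the matter. It is an ambiguity, not a demonstrated contradiction.

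It is also fair to say that the AF bias is probably modest with several years of follow-up. Death is a censoring event in the cause-specific model, so having to survive the gap does not by itself lower the CRAO rate. The downward bias needs gap CRAO to be excluded as well.

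**Conclusion.** The AF-arm contradiction is real, concerns the primary analysis and does not depend on any assumed number. The bias is downward if gap CRAO is excluded. In the scenarios with half of AF patients affected, a hazard ratio of 2 falls to between 1.97 and 1.85 at 3 years of follow-up, and to 1.78 with a 3-month gap at 1 year. The control wording needs clarifying.

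Three stronger readings are not supported:

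- A reader might apply the whole gap to the whole AF arm and infer a rate loss of 3%, 8% or 14% for gaps of 1, 3 or 6 months at 3 years (3/3.083, 3/3.25, 3/3.5). That assumes that every AF patient has a gap, which the inpatient route contradicts.
- A reader might treat the entire control shift as event-free and infer an inflation of 7/5 = 1.4 or 9.5/5 = 1.9. The exclusion reaches back only 12 months and earlier CRAO would count as events, so the factor is about 1.1, and only on the first-eligible-year reading.
- A reader might infer confounding by calendar time because index year is not among the listed covariates. The eligibility section calls the control date a matched one, an article may omit matching details, and no imbalance is shown.

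**What to change.** In Regression modeling (aim 1), item a, replace the first AF claim with the qualifying date from Inclusion and exclusion criteria (Aim 1). State that AF diagnosis in the CRAO exclusion and in the covariate rule means that same date. For controls, state in item a, Adjustment covariates and the Table 3 title that the index date is July 1 of the randomly drawn year, as in Analytical cohort. Use these two dates for eligibility, look-back, propensity score and survival time. This costs a few lines of wording and no new data, and should be settled before the primary analysis is run.

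Optionally, add index calendar year to the Aim 1 propensity score or match on it. This would give the matched index date a stated basis across 2000–2020 and the 2015 change of coding system. The cost is one variable already in the data.

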### Statistical analysis plan

#### Re-estimation of propensity scores and overlap weighting

To adjust for the observed confounding and focus on the patient population in clinical equipoise, we will first re-estimate the propensity scores in the matched sample and then apply propensity score overlap weighting [25–27] to ensure exact balance of baseline covariates between patients with and without AF.

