#### Descriptive analysis

Using the weighted analytic cohort, we will calculate means with standard deviations and medians with interquartile ranges to summarize the distribution of continuous, normally distributed variables, and medians with interquartile ranges to summarize the distribution of continuous, not normally distributed variables. We will summarize categorical data using counts with percentages. Data will be stratified by presence of atrial fibrillation and include key demographic and clinical factors. For Aim 2, we will additionally summarize anticoagulant usage patterns among patients with atrial fibrillation, including class of agent utilized (DOAC vs. warfarin), number of monthly fills per calendar year, and duration of exposure in months. Table shells are provided in Tables 3–5.

**Table 3 pone.0296251.t003:** Characteristics of the overlap-weighted primary analysis cohort defined at first date of meeting study eligibility.

Characteristic	Total Sample (N = xxxx)	Patients with AF (n = xxxx)	Patients without AF (n = xxxx)	Standardized Difference
Age, mean (SD)				
Women, n (%)				
Race/ethnicity, n(%)				
Asian/Pacific Islander				
Black, non-Hispanic				
Hispanic				
White, non-Hispanic				
Comorbidities (n, %)				
Cerebrovascular Disease				
Chronic Kidney Disease				
Congestive Heart Failure				
Coronary Artery Disease				
Diabetes Mellitus				
Hyperlipidemia				
Hypertension				
Peripheral Vascular Disease				
Smoking				

**Table 4 pone.0296251.t004:** Characteristics of the secondary analysis (Part-D enrolled) cohort defined at first date of meeting study eligibility.

Characteristic	Total Sample (N = xxxx)	Patients with at least one fill for anticoagulant (n = xxxx)	Patients without any anticoagulant use (n = xxxx)	Standardized Difference
Age, mean (SD)				
Women, n (%)				
Race/ethnicity, n(%)				
Asian/Pacific Islander				
Black, non-Hispanic				
Hispanic				
White, non-Hispanic				
Comorbidities (n, %)				
Cerebrovascular Disease				
Chronic Kidney Disease				
Congestive Heart Failure				
Coronary Artery Disease				
Diabetes Mellitus				
Hyperlipidemia				
Hypertension				
Peripheral Vascular Disease				
Smoking				
Antiplatelet agent use				
Oral anticoagulant use				
Lipid-lowering agent				
Oral hypoglycemic agent				
Oral antihypertensive agent				

**Table 5 pone.0296251.t005:** Anticoagulation usage patterns among patients with atrial fibrillation with at least one Part D fill for an anticoagulant medication.

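### The Aim 1 sequential adjustment starts after matching and overlap weighting, so it cannot show the sources of measured confounding that it is meant to show

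*Protocol article*

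**What the plan says.** The protocol article fixes this order of operations for Aim 1.

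- **Analytical cohort:** "the final control group will be selected using propensity score matching to the AF cases".
- **Re-estimation of propensity scores and overlap weighting:** scores are estimated again in the matched sample and overlap weights applied "to ensure exact balance of baseline covariates between patients with and without AF".
- **Regression modeling (aim 1), item b:** "a weighted, unadjusted cause-specific hazard model will be fit with AF as the univariable predictor".
- **Item c:** "a weighted cause-specific hazard model, clustered by state, and adjusting for age, sex, race, cardiovascular comorbidities will be fitted".
- **Item e:** the primary model is overlap-weighted, with "propensity scores derived from the adjustment covariates previously described as predictors for the presence of atrial fibrillation". Results are reported with sequential adjustment, and the reason given is: "We employ this sequential adjustment strategy to provide insight as to sources of measured confounding".

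Table 7 has an Unadjusted and an Adjusted column. Its footnote, which describes overlap weighting, is attached to the Adjusted column only. Table 6 is titled as crude and adjusted rates. No hazard ratio from the unmatched cohort is planned anywhere in the article.

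**The concern.** A covariate confounds the AF–CRAO association only if it is distributed differently in the two groups. The plan removes that difference by matching, and again by weighting, before it fits the first hazard ratio. Adding the same covariates afterwards cannot reveal what they contributed to the crude association.

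This matters because the Introduction faults the earlier insurance-based cohort for not adjusting for vascular risk factors, and Aim 1 asks whether AF is a risk factor independent of them. Readers will want to see how much of the crude association those factors explain. Near-identical unadjusted and adjusted hazard ratios would invite the conclusion that measured confounding is negligible, whatever its true size. Rates and ratios from the matched sample that are labelled crude or unadjusted would be misread in the same way.

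**Working it through.** The article gives no figure for the sequential adjustment, so there is none to reproduce. The only input taken from it is the unexposed CRAO rate of 11/100,000 per year (Sample size calculation). All other inputs are assumptions.

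**1. Why weighting removes the signal.** Let A be AF status, e the fitted logistic score and x a covariate in it. The logistic score equation is Σ(A − e)x = 0. Because A − e = A(1 − e) − (1 − A)e, it follows that Σ A(1 − e)x = Σ (1 − A)e·x. The weights 1 − e (AF) and e (controls) are the overlap weights, so the weighted means of x are equal. Item c then adds covariates whose weighted means already agree.

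**2. Size at the start of follow-up.** Take three independent binary confounders with prevalences 0.5, 0.4 and 0.2. Each has odds ratio 3 with AF and hazard ratio 3 with CRAO; AF probability is 3% with no factor present.

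| Factors present | Share of pool | P(AF) | CRAO multiplier |
|---|---|---|---|
| 0 | 0.24 | 0.0300 | 1 |
| 1 | 0.46 | 0.0849 | 3 |
| 2 | 0.26 | 0.2177 | 9 |
| 3 | 0.04 | 0.4551 | 27 |

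- Mean multiplier in AF: Σ share × P(AF) × multiplier ÷ Σ share × P(AF) = 1.1253 ÷ 0.1211 = 9.30.
- Mean multiplier in controls, with 1 − P(AF): 3.9147 ÷ 0.8789 = 4.45.
- Crude HR at true HR 1: 9.30 ÷ 4.45 = 2.09.
- After ideal matching both means are 9.30, so the ratio is 1. After overlap weighting both groups have mass share × P(AF) × (1 − P(AF)), so the ratio is again 1.

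**3. Over 15 years of follow-up.** Base mortality is 4% per year, multiplied by 1.5 per factor. The models are expected-count piecewise-exponential fits.

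| True HR | Confounder effects | AF mortality HR | Crude, unmatched | Weighted unadjusted | Weighted adjusted |
|---|---|---|---|---|---|
| 1 | 3 | 1.0 | 2.06 | 1.00 | 1.00 |
| 1 | 3 | 1.5 | 1.95 | 0.95 | 1.00 |
| 1 | 2 | 1.5 | 1.32 | 0.96 | 1.00 |
| 2 | 3 | 1.5 | 3.89 | 1.89 | 2.00 |

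Adjusting in the unmatched cohort returns the true HR in every row, so a sequence started there does show the confounding. At true HR 1 and AF mortality HR 1.5, shorter follow-up shrinks the drift. The weighted unadjusted HR is 0.98 at 5 years and 0.985 at 3 years with effects of 3, and 0.98 and 0.99 with effects of 2.

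**4. A different confounding model.** This uses a normally distributed comorbidity score, true HR 1.5, 10 years and CRAO at 11/100,000 per year. Without death, the crude HR ran from 1.91 to 4.57 as confounding rose, while the weighted step moved the log-HR by at most 0.001. With comorbidity-dependent mortality doubled by AF, the weighted unadjusted HR was 1.28 to 1.43 against 1.50 adjusted. That is an upward step of 1.50/1.43 = 1.05 to 1.50/1.28 = 1.17.

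**5. If the first model is matched but unweighted.** I simulated 1:1 matching at three confounding strengths (true HR 1.5, no death, outcome rate 0.2% per year, 150,000 subjects, 6 runs each). The crude HRs were 1.95, 2.80 and 4.42. Matched unweighted and weighted unadjusted HRs were the same to two decimals: 1.46, 1.50 and 1.49.

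**6. Control outcomes.** Stroke (1.5% per year assumed) and UTI (5% per year assumed) use the same modeling. At true HR 1.5 without death, adjustment raised the log-HR by 0.01 to 0.09 through non-collapsibility alone. At true HR 1 without death it did not move.

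**The case against.** **The starting point is not fully settled.** The Table 7 footnote ties weighting to the Adjusted column, and Tables 6 and 7 list an overlap-weighted CRAO row apart from the primary-diagnosis row. Both suggest that some estimate is unweighted. This stands as a conflict with item b. It does not rescue item e, because an unweighted start is still matched. The article states no caliper or balance criterion, so some imbalance may survive matching and an unweighted-to-weighted step could show that remnant. It still could not show the confounding present before matching.

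**A condensed article may leave the model list to a fuller plan.** That would answer an omission. Here the article itself fixes the order and states a purpose that this order cannot serve.

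**The inference is untouched.** This is correct. A reader might infer that the primary Aim 1 estimate is biased, but nothing here supports that: the weighted, adjusted model returned the true HR throughout the deterministic calculations.

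**A reader might also infer that the sequence will point in the wrong direction.** That needs excess AF mortality acting on covariate-dependent risk, positive confounding and long follow-up. The article gives a figure for none of these, and without excess AF mortality the sequence does not move. Nor can all residual movement be put down to death, since non-collapsibility contributes for stroke and UTI.

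**The weighted Table 3 may look like a further defect.** It is not. A balance table after weighting is a standard check, and the Univariable analysis section plans standardized differences without restricting them to weighted data.

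**Conclusion.** The point holds as a mismatch between a stated purpose and the planned analysis. With no differential mortality, the reported CRAO hazard ratio will barely move, whether the crude association is inflated by a third or several-fold. With assumed excess, covariate-dependent AF mortality it may drift by about 1% to 17% over the settings tried, for reasons other than baseline confounding. The sizes rest on assumed confounder strengths, mortality and follow-up; that balanced covariates cannot display their earlier confounding does not. The conflict between item b and the Table 7 footnote is separate and also needs resolving. This should be corrected before analysis, but it does not threaten the primary result.

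**What to change.** 1. Reconcile item b with the Table 7 footnote, so that it is clear whether the Unadjusted column is weighted.
2. Start the reported sequence with the crude HR and crude rates in all eligible AF cases against all eligible controls, before matching.
3. Add covariate blocks in that cohort: demographics, then vascular risk factors, then remaining comorbidities.
4. End with the primary matched, overlap-weighted HR, unchanged.
5. In Tables 6 and 7, label figures from the matched sample as matched, not crude.
6. Show standardized differences before matching beside the weighted ones.

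At minimum, withdraw the item e claim and describe the step from item b to item c as covariate adjustment of an already balanced sample.

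The cost is protocol wording, relabelled table shells and a few extra model runs on the control pool that the Analytical cohort section already builds.
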